### Objective of the study

The primary objective of this trial is the determination of the single fraction radiation dose, measured by the number of tumor infiltrating T-cells in the tumor. Secondary molecular objectives are the T cell activity in the resected tumor specimen, the density of regulatory T cells, and the frequency of tumor reactive T cells in blood and bone marrow in correlation with changes in the level of proteins involved in immune response or angiogenesis and transcriptomics in whole blood cells. Further clinical secondary objectives are acute radiogenic toxicity, postoperative morbidity and mortality, local control, recurrence patterns, overall survival and quality of life. All clinical secondary objectives are presented in Table 2.

**Table 2 T2:** Secondary endpoints

Secondary endpoints
• Local control and recurrence patterns of colorectal liver metastasis • Progression free survival • Surgical morbidity in patients undergoing liver resection who received this protocol treatment • 30 day postoperative mortality • Radiation toxicity • Quality of life according to EORTC QoL questionnaire after 3 and 6 months

Currently, 35 patients are randomized. The duration of the trial is expected to last four more months. Usually, two patients per month can be enrolled into this study. Evaluation and reporting of the clinical and laboratory results will be done within three months after the end of recruitment and closing of the database.

### Statistical analysis

This randomized controlled trial is planned as a comparison of four parallel groups:

Group 1: Dose = 0 Gy (control); Group 2: Dose = 0.5 Gy; Group 3: Dose = 2 Gy and Group 4: Dose = 5 Gy.

Aim of the study is to determine the maximum active radiation dose with three different doses. This will be carried out hierarchically in two consecutive steps.

1. Step: Comparison of the three doses against the control group ("Many-to-one" comparison after Dunnet)

2. Step: Comparison of the three doses among each other ("all-subset" comparison)

Each of the two steps happens on multiple levels of significance with a p-value less than 0.05. The power of each step should be at least 80%.

Based on achieved information of a study by Galon et al. [20] in CRC patients, the density of tumor infiltrating T cells is a relevant prognostic parameter. Patients with a good prognosis had a mean of x-good = 600 CD8 T cells/mm^2^, the group with a bad prognosis had a mean of x-bad = 370 CD8 T cells/mm^2^. The standard deviation in both groups was 50/mm^2^. Further analysis revealed that patients with x = 300 tumor infiltrating CD8 T-cells/mm^2 ^in tumor tissue had a significantly better prognosis. Given this background, a clinical relevant difference between 100 and 200 CD8 T-cells/mm^2 ^seems plausible. The number of cases should be sufficient for a difference of 150 CD8 T-cells/mm^2^.

For the first step, 32 analyzable patients will be needed which equals eight patients for each of the four groups. The nominal power of ANOVA is around 90%. For the second step (comparison of the best group, Hsu 2006), the power for n = 32 is 95%. Not all of the randomized patients could be analyzed with respect to the primary objective. A failure of 10 - 15% has to be assumed due to poor tissue quality or technical problems. Therefore, 40 patients should be randomized.

The calculated number of cases was carried out with PASS 2005 (Hintze J, 2004): NCSS and PASS. Number Cruncher Statistical Systems. Kaysville, Utah. http://www.ncss.com) with the procedure for multiple comparisons by Jason C. Hsu (1996) (Multiple Comparisons: Theory and methods, Chapman & Hall). The analysis of the primary objective results confirmatory on a multiple level of significance of p < 0.05 by ANOVA based on the calculated numbers of cases. The analysis of the secondary objective results is descriptive by determining the means, the quartiles as location parameter and the standard deviation and range as dispersion parameters. The correlation between the parameters will be quantified by the Pearson or Spearman test. The EORTC QLY-C30 single-item and multi-item subscales will be scored and linearly transformed according to algorithms recommended by the EORTC. Using two-sample t-tests for continuous and Pearsons's X^2 ^Test for categorical variables, the intervention and the control arms will be compared in terms of clinical characteristics at time of randomisation and in terms of baseline QOL scores. Repeated measures ANOVA will be applied to test for changes in the continuous secondary endpoints - e.g. plasma cytokine levels- as a function of treatment arms.

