**Methods/Design:**

This is an investigator-initiated, prospective randomised, 4-armed, controlled Phase I/II trial. Patients undergoing elective hepatic resection due to colorectal cancer liver metastasis will be enrolled in the study. Patients will receive 0 Gy, 0.5 Gy, 2 Gy or 5 Gy radiation targeted to their liver metastasis. Radiation will be applied by external beam radiotherapy using a 6 MV linear accelerator (Linac) with intensity modulated radiotherapy (IMRT) technique two days prior to surgical resection. All patients admitted to the Department of General-, Visceral-, and Transplantion Surgery, University of Heidelberg for elective hepatic resection are consecutively screened for eligibility into this trial, and written informed consent is obtained before inclusion. The primary objective is to assess the effect of active local external beam radiation dose on, tumor infiltrating T cells as a surrogate parameter for antitumor activity. Secondary objectives include radiogenic treatment toxicity, postoperative morbidity and mortality, local tumor control and recurrence patterns, survival and quality of life. Furthermore, frequencies of systemic tumor reactive T cells in blood and bone marrow will be correlated with clinical outcome.

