### Study design

This single fraction radiation on colorectal liver metastases trial is a registered (ClinicalTrials.gov - NCT01191632), investigator-initiated, prospective, randomized controlled phase I/II trial to evaluate the optimal neoadjuvant, single fraction radiation dose for patients undergoing resection for colorectal liver metastases in curative intent. Patients will be randomised either to the control group -receiving no radiation- or the three treatment groups - receiving 0.5 Gy, 2 Gy or 5 Gy single fraction radiation to the metastasis 48 h prior to the operation. The treatment is offered to a heterogeneous group of patient of both sexes, covering a wide range of comorbidities. For the irradiation a highly conformal dose distribution to the tumor with 1 cm safety margin is delivered using a 6 MV LINAC and intensity modulated radiotherapy (IMRT) treatment application. After inclusion of 20 patients an interims analysis will be performed. The final analysis will be performed within three month of the inclusion of the last patient. The trial design will not be changed without prior agreement of the ethics committee.

Translational studies will be carried out by the Department of Translational Immunology of dkfz, the Radiation Oncology Departments of German Cancer Research Center (DKFZ) and the Surgery Departments of the University Hospital. This trial is an investigator-initiated trial and is coordinated by the Department of General-, Visceral- and Transplantation Surgery and the Radiation Oncology Department of DKFZ. The Radiation Oncology Department of DKFZ is responsible for the overall trial management, trial registration, database management, quality assurance including monitoring and scientific program of all trial related meetings. The methods and the study design of this trial have the same structure as the previously published study protocol for patients with pancreatic cancer (BMC Cancer 2011; 11:34) [19].

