### Follow up

A routine follow up for cancer patients will be done including physical examination of the patients, tumor markers (CEA), CT/MRI, chest X-ray every three months. Disease-free survival and overall survival will be recorded. Notably, the further clinical management and postoperative treatment of the patients will not be influenced by the results of this study. The decision whether patients will receive an adjuvant treatment (e.g. chemotherapy) is left to the discretion of the treating oncologist.

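### The descriptive rule for secondary results (mean, quartiles, SD, range) is unqualified, so read literally it covers censored survival and local-control times, for which it is unsuitable

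*Protocol article*

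**What the plan says.** All references are to the protocol article.

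- **Rule for secondary results** (Statistical analysis): "The analysis of the secondary objective results is descriptive by determining the means, the quartiles as location parameter and the standard deviation and range". On association, the same section adds: "The correlation between the parameters will be quantified by the Pearson or Spearman test".
- **Other methods in that section:** EORTC scoring for quality of life, t and chi-square tests for characteristics at randomisation and baseline quality of life, and repeated measures ANOVA for continuous secondary endpoints. None of these handles censored times.
- **Endpoints the rule would cover:** Objective of the study names "local control, recurrence patterns, overall survival and quality of life" among the clinical secondary objectives. Table 2 in that section lists "Progression free survival". The Follow up section states: "Disease-free survival and overall survival will be recorded".
- **Timing:** Study design says "The final analysis will be performed within three month of the inclusion of the last patient". Objective of the study says "Usually, two patients per month can be enrolled into this study".
- **Link to outcome:** the abstract says that "frequencies of systemic tumor reactive T cells in blood and bone marrow will be correlated with clinical outcome".

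**The concern.** A time to recurrence or death is known in full only for patients who have had the event by the data cut. For the others only a lower bound is known. A plain mean of the recorded times treats these bounds as event times and is too low. A mean over the events alone is lower still. The SD and range have the same fault, because the largest recorded values are set by date of entry and date of cut. Quartiles can be estimated from censored data, but the article does not say that this is how they will be obtained.

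At stake are the descriptive summaries of survival and local control, which are the clinical results that readers will look for. Followed literally, the rule would give figures in months that look like survival times but mainly measure how long patients had been in the trial.

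**Working it through.** The article states no figure for these endpoints, so there is nothing to reproduce. The check has two parts.

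**1. Does the rule reach censored endpoints?** The rule is attached to the secondary objective results without restriction. Local control and overall survival are named as secondary objectives, and progression-free survival is in Table 2. No other sentence in the article gives a method for them. Read literally, the rule covers them.

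**2. How much would it matter?**

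Inputs from the article:
- 40 patients to be randomised (Statistical analysis).
- Two patients per month (Objective of the study), so accrual takes 40 / 2 = 20 months.
- Final analysis within 3 months of the last inclusion (Study design). Taking the full 3 months, follow-up C runs from 3 to 20 + 3 = 23 months.

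Assumptions not in the article: C is uniform over 3 to 23 months, and event times T are exponential with median m, taken from 9 to 40 months because the article gives none.

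Formulas, with λ = ln 2 / m, a = 3 and b = 23:
- True mean = 1/λ
- Proportion censored p = (e^(−λa) − e^(−λb)) / (λ(b − a))
- Mean recorded time E[min(T, C)] = (1 − p)/λ

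For m = 12:
- λ = 0.6931 / 12 = 0.05776, so the true mean is 17.3 months.
- p = (0.8409 − 0.2649) / (0.05776 × 20) = 0.5760 / 1.1552 = 0.499.
- Mean recorded time = (1 − 0.499) × 17.31 = 8.7 months.

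The same formulas over the assumed range:

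| Assumed median (months) | True mean | Mean recorded time | Censored |
|---|---|---|---|
| 9 | 13.0 | 7.7 | 40% |
| 12 | 17.3 | 8.7 | 50% |
| 18 | 26.0 | 9.8 | 62% |
| 24 | 34.6 | 10.5 | 70% |
| 40 | 57.7 | 11.4 | 80% |

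The true mean rises more than fourfold down the table (57.7 / 13.0 = 4.4), while the recorded mean rises by about half (11.4 / 7.7 = 1.5). The recorded mean stays below the average follow-up of (3 + 23) / 2 = 13 months, whatever the outcome.

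A simulation of 40 patients entering every half month (follow-up 3 to 22.5 months, 4,000 repetitions) agrees:
- The mean recorded time was 7.6 to 11.2 months, with 41% to 81% censored, over the same medians.
- The mean over events alone was 5.8 to 7.2 months.
- In the same simulated data, Kaplan-Meier at 12 months was practically unbiased: 0.499 against a true 0.500 for a 12-month median, and 0.707 against 0.707 for 24 months.
- With a minimum follow-up of 12 months instead of 3, the mean recorded time was still too low: 10.3 to 17.9 months against 13.0 to 57.7.

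**The case against.** The strongest reply is that the sentence was never meant for survival. Taken literally it would also give an SD and range for 30-day mortality, which cannot be intended. The same section later speaks of continuous secondary endpoints, so the authors recognise a subset. A condensed article also commonly leaves Kaplan-Meier and censoring rules to the full protocol or analysis plan. This stands in part: the absence of those methods is not itself the finding. What remains is that the article states a rule, attaches it to the secondary results without limit, and that rule is wrong for some of the endpoints it lists.

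Four stronger readings are tempting, and the article does not support them.

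- **That every secondary endpoint gets only mean, SD and range.** The rule includes quartiles, and continuous endpoints also get repeated measures ANOVA.
- **That the T-cell and outcome correlation is bound to be uninterpretable.** The sentence on Pearson and Spearman refers only to unspecified parameters. Where Objective of the study defines the correlation, it links T-cell frequencies with protein levels and transcriptomics, for which these methods are suitable. Only the abstract mentions clinical outcome, without naming survival or a method.
- **That a treatment effect would be masked.** Under the same assumptions, with a 12-month control median, a hazard ratio of 0.6 (a true ratio of means of 1 / 0.6 = 1.67) would show as a ratio of recorded means of about 1.16. But the article plans no between-arm comparison of survival and calls the secondary analysis descriptive.
- **That the size of the bias is known.** The medians are assumed and the cut is not settled. Objective of the study puts evaluation within three months of the end of recruitment and closing of the database, and visits are scheduled up to seven months after surgery. A later cut lessens the bias without removing it.

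Recurrence patterns may also be meant as a categorical description of site, in which case censored-time methods do not apply to that item.

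**Conclusion.** The point holds in a limited form. The stated rule, read literally, applies mean, SD and range to local control, progression-free or disease-free survival and overall survival, and for these endpoints it would mostly summarise length of follow-up. With a 12-month median, exponential times and follow-up uniform over 3 to 23 months, the recorded mean is about half the true mean. The median and the distribution are assumptions, and the follow-up range depends on the article's accrual rate and its earlier statement of analysis timing. The direction of the bias does not depend on the assumed median, but its size does.

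The correlation point is conditional: it applies only if the abstract's clinical outcome includes survival or recurrence.

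Two inconsistencies are editorial. Table 2 says progression-free where Follow up says disease-free. Overall survival is missing from Table 2, although the text says that the table presents all clinical secondary objectives.

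The primary endpoint, the sample size and the confirmatory analysis are unaffected.

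**What to change.** - Limit the sentence on means, quartiles, SD and range to continuous secondary measures.
- Summarise progression-free or disease-free survival and overall survival per arm by Kaplan-Meier: fixed-time probabilities with confidence intervals, and quartiles where estimable.
- Summarise local recurrence by cumulative incidence, with death as a competing event.
- Report binary outcomes, such as 30-day mortality, as counts and proportions.
- If T-cell frequencies are to be related to survival or recurrence, replace Pearson or Spearman for that purpose with a censoring-aware method, such as exploratory univariable Cox regression. State that few events are expected among 40 patients.
- State the date of the data cut for these endpoints.
- Choose one name and definition for the recurrence endpoint, use it in Table 2 and Follow up, and reconcile Table 2 with the text on overall survival.

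The cost is a few sentences of analysis wording and standard software. No further patients are needed. The methods use event and last-contact dates, which the recording of survival at follow-up should already provide.

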**Exclusion criteria**

Previous radiotherapy to the upper abdomen
Participation in other therapeutical trials
Liver cirrhosis
Pregnancy
No willingness on regular follow up care
Any extrahepatic disease

Patients who meet the eligibility criteria and provide written informed consent are randomly allocated to either study intervention to balance treatment groups for all known and unknown potentially confounding factors. A block randomisation list is created via a computer system. Patients are randomised using consecutively numbered opaque envelopes prepared and sealed by an independent study nurse. The envelopes will be opened sequentially only after the participant's name is written on the appropriate envelope. Neither the screening investigators nor the investigators who inform the potential participants about this trial and enrolling the patients, have any knowledge of the block randomisation list or the previous allocations to treatment. There is no stratification for randomisation.

After informed consent, patients are randomized either to the control group - receiving no radiation - or the three irradiation treatment groups. Within the irradiation treatment groups patients will receive 0.5 Gy, 2 Gy or 5 Gy single fraction radiation 48 h prior to resection. After the adjustment of an individual positioning device, computed tomography and, if needed, magnetic resonance imaging (MRI) treatment planning examinations are performed. After 3D inverse treatment planning and plan optimizing using VIRTUOS and KONRAD software, intensity modulated radiation therapy will be administered using five to nine 6 MV linear acceleration (LINAC) photon beams. Immediately prior to the irradiation the setup error of the patient will be determined via In-Room-CT, and corrected if necessary.

The first blood sample will be obtained (54 ml) before radiation, a second just prior to the start of the operation. A bilateral bone marrow sample (27 ml each) will be taken from both iliac crests after induction of general anaesthesia just before skin incision. Bone marrow sampling is optional for the patient. EDTA will be used as anticoagulant for bone marrow and blood samples. After hepatic resection a part of the tumor will be immediately removed and stored at -80°C for further analyses.

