On the postoperative day seven and at the follow-up/restaging visits (4 weeks postoperatively, four and seven months postoperatively) additional venous blood samples (54 ml) will be obtained. Quality of Life will be tested using the EORTC QLQ C-30 at four months and seven months postoperatively. Clinical examination will be performed and blood samples will be obtained by the investigators at all visits.

Curative surgery requires complete resection of all liver metastases, regardless of size, number, distribution, or width of resection margin. Liver operation will be carried out under low central venous pressure using a Péan clamp, ultrasonic dissector or vascular stapler. An intraoperative ultrasound of the liver will be performed in all patients to assess the relationship of the lesions to major vessels and to rule out additional lesions. The Brisbane 2000 terminology of hepatic anatomy and resections will be applied [16].

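### If all six blood samples enter one classical repeated measures ANOVA, patients with any gap drop out and the pre-radiation value is used inefficiently; a mixed model avoids both losses

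*Protocol article*

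**What the plan says.** The Statistical analysis section names the method for serial secondary measures in one sentence: "Repeated measures ANOVA will be applied to test for changes in the continuous secondary endpoints". The sentence gives plasma cytokines as the example and makes the comparison by treatment arm. Earlier in the same paragraph it states: "The analysis of the secondary objective results is descriptive". Only the primary analysis is called confirmatory.

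The sampling schedule stands in Methods/Design, Trial population and patient recruitment, in the text after the eligibility table. It begins: "The first blood sample will be obtained (54 ml) before radiation, a second just prior to the start of the operation". The later draws follow: "On the postoperative day seven and at the follow-up/restaging visits (4 weeks postoperatively, four and seven months postoperatively) additional venous blood samples". That makes six draws: before radiation, before surgery, day 7, 4 weeks, 4 months and 7 months.

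On timing, the Study design section places the final analysis no later than three months after the last patient's inclusion. The Objective of the study section reports 35 patients already randomised, a usual accrual of two per month and about four months still to run. It counts its three months for evaluation from the end of recruitment and database closure. The target is given as: "Therefore, 40 patients should be randomized".

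The article does not say which visits enter the repeated measures analysis, how missing samples are handled, or whether the pre-radiation value is a response or a covariate.

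**The concern.** Classical repeated measures ANOVA works on complete rows: a patient who lacks one of the modelled visits contributes nothing, not even to comparisons between visits that were observed. With six visits spread over more than seven months, and a final analysis that can precede the last visit of late recruits, incomplete rows are to be expected. A patient with good samples before radiation and before surgery could be lost to the early comparison only because the seven-month visit has not yet come round.

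A test for changes also most naturally places the pre-radiation value among the repeated responses. In a randomised trial that value is more useful as a covariate.

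At stake is the precision of the arm comparisons on serial blood measures, with about 10 patients per arm. There may also be bias, if patients with complications or recurrence are the ones who miss visits. The gaps caused by the analysis date depend on when a patient was enrolled, so dropping those patients mainly costs precision.

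**Working it through.** **1. The plan's own figure.** The article gives no power, sample size or missing rate for this analysis. Its only related figure is the 40 to be randomised for 32 analysable:

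- 10% failures: 32 / 0.90 = 35.6, so 36
- 15% failures: 32 / 0.85 = 37.6, so 38
- 20% failures: 32 / 0.80 = 40

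So 40 covers the stated 10–15% with a small margin. That allowance is for tissue quality and technical failure in the primary endpoint, not for missed blood samples.

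**2. Loss from the analysis date.** If the analysis takes place three months after the last inclusion, a patient included *m* months before the last one has at most *m* + 3 months of follow-up. The seven-month sample needs *m* + 3 ≥ 7, so *m* ≥ 4. Time between inclusion and surgery makes this slightly stricter.

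- At two per month: 2 × 4 = 8 of 40 (20%) lack it, leaving 32.
- If the outstanding 40 − 35 = 5 patients are spread over the four remaining months: 5 of 40 (12.5%) lack it, leaving 35.
- If the data close *x* months after the last inclusion, the number at two per month is 2 × (7 − *x*): 8 at *x* = 3, 4 at *x* = 5, none at *x* = 7.
- The four-month sample needs *m* ≥ 1, so about 2 × 1 = 2 of the same patients lack that one as well.

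**3. Loss from random gaps (assumption).** With independent missingness *p* at each of six samples, expected complete rows are 40 × (1 − *p*)^6:

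| *p* | complete of 40 | loss |
|---|---|---|
| 1% | 37.7 | 6% |
| 2% | 35.4 | 11% |
| 5% | 29.4 | 26% |
| 10% | 21.3 | 47% |

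If gaps arise only because patients leave and do not return, 10–15% dropout loses just that: 36 to 34 remain.

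**4. Both together.** With 8 lost to the analysis date and 5% missing per sample: 32 × 0.95^6 = 23.5, about 6 per arm.

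**5. Baseline, one later value.** With unit variance and correlation ρ, the change score has variance 2(1 − ρ) and the baseline-adjusted value 1 − ρ². The ratio is (1 + ρ)/2: 0.65, 0.75, 0.85 and 0.95 at ρ = 0.3, 0.5, 0.7 and 0.9. A change analysis of 40 is then worth about 40 × 0.65 = 26 to 40 × 0.95 = 38 patients.

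**6. Baseline, six visits, nothing missing.** Assume a common correlation ρ and a constant shift after radiation. Information per patient is:

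- mean of five later values, adjusted for baseline: 1 / [ρ + (1 − ρ)/5 − ρ²]
- arm main effect over all six visits: (5/6)² / [ρ + (1 − ρ)/6]
- later mean minus baseline: 1 / [(1 − ρ)(1 + 1/5)]

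At ρ = 0.5 these are 1/0.35 = 2.86, 0.694/0.583 = 1.19 and 1/0.60 = 1.67. Relative to the adjusted analysis, the main effect carries 0.42 and the change contrast 0.58 of the information. At ρ = 0.3 the two figures are 0.58 and 0.42; at ρ = 0.7 they are 0.25 and 0.75. The precision cost of using baseline as a response therefore exists even when every sample is obtained.

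**The case against.** The strongest reply is that the article only names a method. Row deletion, all six visits in one model, and baseline as a response are inferences. No text says that cytokines are assayed at every draw, and a full protocol or analysis plan that is not shown could settle all three. This stands, so the point has to be conditional. It remains that the named method, in its classical form, fits the stated schedule poorly.

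A reader might go further and infer that the plan discards every patient with one missing sample and so wastes a large share of the trial. The documents do not support that. The primary endpoint is T-cell number in the resected tumour, measured once, and this method does not touch it. The missing rates and correlations above are assumptions; at 1–2% missing per sample the random loss is only 6–11%. Nor do the documents make the blood time course the main supporting evidence: T-cell activity and regulatory T-cell density in the specimen are listed first among the secondary molecular objectives.

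The analysis date is also open to some extent, because the Objective of the study section refers to database closure and so allows a later cut. A mixed model cannot create seven-month data that do not yet exist; it keeps those patients in for their earlier visits.

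Sphericity (equal variance of all pairwise visit differences) is doubtful over such uneven intervals, but standard corrections exist and the point does not rest on it.

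**Conclusion.** The point holds as a conditional improvement to a secondary analysis, of minor to moderate severity. If all visits enter one classical repeated measures ANOVA, and the analysis takes place three months after the last inclusion, about 5 to 8 of 40 patients (12.5% to 20%) are lost for lack of the seven-month sample alone, and fewer with a later database close. Any further loss depends on an unknown missing rate. If the pre-radiation value is used as one more response, precision is lost even with complete data, by an amount that depends on the unknown correlation. Separately, calling the secondary analyses descriptive and then planning a test on them is a small inconsistency in the text that needs reconciling.

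**What to change.** Replace the repeated measures ANOVA with a mixed model for repeated measures on all available post-radiation samples. Include arm, visit, arm-by-visit interaction and the pre-radiation value as covariate, with Kenward-Roger degrees of freedom. Use an unstructured covariance, and prespecify a simpler fallback suited to unequal spacing, such as compound symmetry or a continuous-time spatial power structure. A plain autoregressive structure does not suit visits that lie days to months apart. Label the p-values exploratory, to agree with the descriptive status of the secondary analyses.

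The cost is a change of wording and slightly more modelling work; no new data are needed. An unstructured covariance over five post-radiation visits has 5 × 6 / 2 = 15 parameters, so with about 10 patients per arm the fallback may well be needed.
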